### Objectives of the Trivalve study

Each aortic valve has its own hemodynamic characteristics related to its geometry and each patient has their own morphology (weight, size, anatomy of aortic valve), as well as different physiological and pathophysiological conditions (ejection fraction, size and degree of calcification of the aortic annulus, degree of left ventricular hypertrophy and so on). Consequently, the choice of valve prosthesis and the surgical implantation technique are the only two directly adjustable variables; nonetheless, current literature does not provide clear differences among available bioprostheses.

The main objective of this study is to measure the hemodynamic performance of the three aortic bioprostheses: the Trifecta valve (St. Jude Medical, Minneapolis, MN, USA), the Mitroflow valve (Sorin Group, Saluggia, Italy), and the Magna Ease valve (Edwards Lifesciences, Irvine, CA, USA) Table 1.

**Table 1 T1:** Bioprosthesis characteristics

**Bioprosthesis type**	**Manufacturer**	**Valve diameters (mm)**
Trifecta	St. Jude Medical, Minneapolis, USA	19 to 29
Mitroflow	Sorin Group, Saluggia, Italy	19 to 29
Carpentier-Edwards Magna Ease	Edwards Lifesciences, Irvine, USA	19 to 29

Secondary end points will focus on 1) comparison between the effective aortic orifice area measured by computerized tomography (CT)-scan and echocardiography and the intraoperative measurement performed by a flat-head candle; 2) comparison between the diameter of the aortic orifice measured by a flat-head candle and the size of the implanted bioprosthesis provided by the manufacturer; 3) testing the accuracy of information provided by the manufacturers about bioprosthesis diameters.

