### Postoperative endpoints

All preoperative echocardiography collected measures will be reassessed at day seven and month six after surgery in addition to maximal and mean transvalvular gradients (mmHg). ICU, total hospital stay and any other postoperative complications will be recorded in the postoperative report and in the case-report form.

The primary endpoint is the mean transvalvular gradient (mmHg) six months after surgery. All secondary endpoints are indicated in Table 4.

**Table 4 T4:** Primary and secondary endpoints

	
**Primary endpoint**	Mean transvalvular gradient (mmHg), six months after surgery
**Secondary endpoints**	Effective aortic orifice diameter measured by CT-scan and echocardiography compared with the surgical data (mm)
	Mean transvalvular gradient (mmHg), at day seven after surgery
	Aortic bioprosthesis orifice area (m^2^), six months after surgery
	Diameter of the aortic orifice measured by a flat-head candle compared with the size of the implanted bioprosthesis (mm)

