### Statistical analyses

All analyses will be performed using STATA v11 (StataCorp, College Station, TX, USA). A two-tailed *P*-value of 0.05 will be considered statistically significant. All analyses will be performed on an intention-to-treat (ITT) basis. The number of included patients and the rate of inclusions will be presented over time for each group. The patients will be described and compared between groups at baseline according to the following variables: compliance with eligibility criteria, epidemiological features, clinical features (including echocardiographic) and biological characteristics. The comparison concerning the postoperative means of the transvalvular gradients (measured by echocardiography at six months post surgery) between the three groups will be evaluated using ANOVA followed by the Tukey-Kramer *post hoc* test, or the Kruskal-Wallis nonparametric test if conditions of ANOVA are not met (homoscedasticity studied by Bartlett’s test and normality verify by Shapiro-Wilk) followed by Dunn’s test as appropriate. Comparisons between the groups will be realized systematically 1) without adjustment and 2) when appropriate, after adjustment (by multivariate linear regression model) on factors whose distribution could be unbalanced between the arms despite randomization. Quantitative secondary endpoints (for example hemodynamic data, CT-scan, in-hospital stay) will be analyzed as described above. Categorical parameters (that is, proportion of reoperations) will be compared between the groups using the chi-squared test or Fisher’s exact test, when necessary. To assess the relationships between the quantitative parameters (comparison between aortic orifice measurements by echocardiography, CT-scans, intraoperative measurement using the flat- candle versus the size of implanted valve prosthesis given by the manufacturer), the correlation coefficients (Pearson or Spearman), the Lin concordance coefficient and the intra-class coefficient (ICC) will be calculated. Later on, an ANCOVA could be proposed to consider group effect. The intra-group comparisons related to the quantitative criteria (hemodynamic data by echocardiography on preoperative period and at six months) will be made using paired the ANOVA or Wilcoxon test. Finally, to avoid bias induced by the presence of missing data, particularly with regards to the mean postoperative transvalvular gradient at six months (lost at follow-up or deaths), the primary analysis (ITT with imputation data determined according to quantity and type of missing data) will be completed on a second time by a per-protocol analysis.

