## Discussion

Several studies have emphasized the importance of valve prosthesis hemodynamic performance [7,8], but none has taken into account more than one or two bioprostheses at a time [9,10]. Thus, we strongly believe that a randomized trial, with no direct conflicts of interest with industry, is mandatory to compare the three bioprostheses most commonly implanted in France and all around the world.

Our secondary objective is to compare the reliability of preoperative CT-scan and echocardiography used to assess the size of the aortic annulus in comparison to the surgical measurement. Both techniques (CT-scans and echocardiography) are already successfully used to predict the correct size of the aortic annulus before trans-catheter valve implantation procedures [11]. Another secondary objective, once we have assessed the surgical diameter of the aortic annulus intraoperatively, is to verify the reliability of the prosthesis size provided by the manufacturer. This last point is interesting as it aims to clarify an issue often debated by surgeons who complain to manufacturers that they over- or underestimate valve sizes. Precise information on the size of the implanted bioprosthesis compared to the real dimensions of the aortic annulus will guide cardiac surgeons to choose between these three bioprostheses according to the patient’s morphological characteristics.

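### The sizing analysis commits only to unitless coefficients, so it does not give the direction or size in mm of any over- or understatement for each valve

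*Protocol article*

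**What the plan says.** The question is set in three places in the protocol article.

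- *Objectives of the Trivalve study* lists, as its third secondary item, "testing the accuracy of information provided by the manufacturers about bioprosthesis diameters". The second item compares candle diameter with labelled size.
- *Postoperative endpoints*, Table 4, makes the second item a secondary endpoint in mm: "Diameter of the aortic orifice measured by a flat-head candle compared with the size of the implanted bioprosthesis (mm").
- *Discussion* says that the work should clarify a dispute raised by "surgeons who complain to manufacturers that they over- or underestimate valve sizes", and that the answer should help surgeons choose among the three valves.

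The method is set in *Statistical analyses*. For the echo, CT and "intraoperative measurement using the flat- candle versus the size of implanted valve prosthesis given by the manufacturer" comparisons it says that "the correlation coefficients (Pearson or Spearman), the Lin concordance coefficient and the intra-class coefficient (ICC) will be calculated". Valve type follows in one sentence: "Later on, an ANCOVA could be proposed to consider group effect".

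Two other sentences in that section lie close by. A general rule says "Quantitative secondary endpoints (for example hemodynamic data, CT-scan, in-hospital stay) will be analyzed as described above", which refers back to ANOVA with Tukey-Kramer or Kruskal-Wallis with Dunn. Paired within-group tests are described for echo hemodynamics, before surgery against six months.

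**The concern.** An answer to the sizing question needs a sign (over or under), a size in mm and a named valve. None of the coefficients supplies a sign or a unit. They supply a valve only if computed by valve, which the article does not state. The one model that would bring in valve type is something that may be proposed later.

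At stake is a listed secondary endpoint. A report that follows the committed text could give a moderate concordance and leave the reader unable to say which manufacturer's label runs large, which runs small, or by how much. The method is named for this comparison and does not match the stated aim, so this is more than detail left to an analysis plan that is not shown.

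**Working it through.** **The plan's own figures.** The article gives no figure for the sizing endpoints. The only number used from it is 55 patients per group. That builds on the primary-endpoint calculation, 2 × (5.8 × (1.960 + 1.282) / 4)² = 44.18, which agrees with the stated 44 before the increase for multiple comparisons. Neither number is disputed here.

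**Assumed inputs, not in the documents.** Annulus SD 2 mm, error SD 1 mm, and label = annulus + valve bias + error. The bias of 2 mm equals the gap between the 21 and 23 mm diameters named in *Sample size estimation*.

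**Formulas** (x = candle, y = label):
- Pearson r = cov / √(var x × var y)
- Lin = 2 cov / (var x + var y + (mean x − mean y)²)
- In this two-measurement setting the absolute-agreement ICC equals Lin. The consistency ICC is 2 cov / (var x + var y). The article does not say which ICC is meant.

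The mean difference is absent from r and from the consistency ICC. It enters Lin and the absolute-agreement ICC only as a square. Equality for +b and −b is therefore algebra and does not depend on the assumed SDs.

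**Within one valve.** var x = 4, var y = 4 + 1 = 5, cov = 4.

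| Bias | r | Lin and absolute-agreement ICC | Consistency ICC |
|---|---|---|---|
| 0 | 4/√20 = 0.89 | 8/9 = 0.89 | 0.89 |
| +2 mm | 0.89 | 8/(9 + 4) = 0.62 | 0.89 |
| −2 mm | 0.89 | 8/(9 + 4) = 0.62 | 0.89 |

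**Over all three valves, equal numbers, biases +2, 0, −2 mm.** The variance of the biases is (4 + 0 + 4)/3 = 2.67, so var y = 7.67. The overall mean difference is 0.
- r = 4/√(4 × 7.67) = 0.72
- Lin = 8/(4 + 7.67) = 0.69; both forms of ICC are also 0.69
- Swapping the over- and understated valves leaves every term unchanged. Simulation of 2,000 data sets gave r = 0.72 and Lin = 0.68 in both directions, while the mean signed difference per valve recovered +2.0/0.0/−2.0 and −2.0/0.0/+2.0.
- With biases of +1, 0, −1 mm, var y = 5.67, r = 0.84 and Lin = 8/9.67 = 0.83, again the same when reversed.

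**Dependence on the spread of annulus sizes.** Keep the 2 mm bias and error SD 1 mm within one valve.
- Annulus SD 1.5 mm: Lin = 4.5/(2.25 + 3.25 + 4) = 0.47
- Annulus SD 2 mm: Lin = 0.62
- Annulus SD 3 mm: Lin = 18/(9 + 10 + 4) = 0.78

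The same error in mm gives quite different coefficients.

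**Precision of a signed difference with 55 per valve.** Half-width of the 95% CI = t(0.975; 54) × SD/√55 = 2.005 × SD/7.416.

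| Assumed SD of difference (mm) | Half-width (mm) |
|---|---|
| 1 | 0.27 |
| 1.5 | 0.41 |
| 2 | 0.54 |
| 3 | 0.81 |

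**The case against.** **The general rule might already cover this.** Table 4 gives the endpoint in mm, and quantitative secondary endpoints go to ANOVA with pairwise comparisons. Applied to a label-minus-candle variable, that would yield means in mm by valve. But the article defines no such variable, its examples do not include one, and the rule tests valves against each other, not each valve's bias against zero. The ANCOVA, if done, would give signed offsets between valves, but it is not a commitment. What stands is that the data would allow the right analysis. A reader might infer that the trial cannot answer the sizing question at all; the documents do not support that.

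**The text never says the coefficients are pooled.** This is correct. Pooling is an inference from the deferral of the group effect. Coefficients by valve would identify the valve but still lack sign and mm.

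**The coefficients do react to bias.** This also stands. A reader might infer that opposite errors cancel, or that a biased valve would pass unnoticed behind r = 0.89. Neither follows. Under the assumptions above, opposite errors lower r and Lin from 0.89 to 0.72 and 0.69. For a valve biased by 2 mm, Lin falls to 0.62, and its gap from r signals a systematic shift. Cancellation would occur in a pooled mean difference, which is not planned.

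**Label minus candle is not pure manufacturer error.** This stands too. The implanted size also reflects the surgeon's choice, and the objectives list the candle comparison and the accuracy of manufacturers' diameters separately, although the *Discussion* links them.

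**A condensed article leaves detail to the analysis plan.** That would excuse silence. Here the article names the method for this comparison.

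**Conclusion.** The point holds for the committed sizing analysis: it does not give the direction or the size in mm of any over- or understatement per valve, which Table 4 and the *Discussion* ask for. That conclusion rests on the form of the coefficients. The illustrative values rest on the assumed SDs and biases, and the lack of attribution to a valve holds only if the coefficients are computed over all valves. For CT and echo against the candle, analysis over all patients is suitable, and only the missing sign and mm scale matter.

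The change should be made, but its reach is limited to secondary endpoints. The primary endpoint and the sample size are untouched.

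**What to change.** In *Statistical analyses*, pre-specify the following for the sizing endpoints.

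1. **Label versus candle:** the mean signed difference (labelled size minus candle diameter, mm) with 95% CI and 95% limits of agreement, separately for each valve implanted. State that grouping is by implanted valve, since the article otherwise places all analyses on an intention-to-treat basis.
2. **Between valves:** a linear model of that difference on valve and annulus diameter, as a planned analysis in place of the optional ANCOVA.
3. **CT and echo versus candle:** the same signed difference and limits, over all patients.
4. **Coefficients:** keep Lin and the ICC as supportive, naming the ICC form. Do not use Pearson or Spearman as evidence of agreement.
5. **Interpretation:** state that label minus candle also reflects the surgeon's choice of implanted size. Table 3 records both estimated and implanted valve diameter, so report the difference for each.

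The cost is a change of wording and slightly more analysis work. It needs no new data and no additional patients.

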### Patient’s enrollment and randomization

All patients scheduled for surgical aortic valve replacement by bioprosthesis will be screened according to inclusion and exclusion criteria (Table 2).

**Table 2 T2:** Inclusion and exclusion criteria

	
**Inclusion criteria**	Isolated aortic valve replacement or associated with myocardial revascularization and/or tricuspid valve repair
	Age (> 18 years and < 85 years)
**Exclusion criteria**	Emergency surgery
	Surgery other than full sternotomy
	Heart transplantation
	Any procedure involving the aorta (such as Bentall procedure, surgery for dissection, and so on)
	Redo surgery
	Active infective endocarditis
	Associated mitral valve surgery
	Heart failure (ejection fraction < 40%) or preoperative cardiogenic shock
	Systolic pulmonary arterial pressure > 60 mmHg
	Patient’s protocol refusal
	Pregnancy
	Mentally handicapped patients, pre-existing psychiatric disease or addiction
	Advanced respiratory failure (forced expiratory volume in 1 second or vital capacity below 50% of the predicted)
	Severe renal failure
	History of allergy or intolerance to iodinated contrast infusion
	Patients living more than 100 km away from the investigation center

Patients who have given their signed informed consent to participate in this clinical trial will undergo, preoperatively, a CT-scan and a transthoracic echocardiogram to measure the aortic annulus. Included patients will be randomly allocated to receive one of the three bioprostheses, in a 1:1:1 ratio. When a patient is considered eligible and informed consent has been obtained, randomization will be performed automatically (using STATA software (StataCorp, College Station, TX, USA) before surgery by an independent biostatistician. No stratification will be done. The selected bioprosthesis will be implanted.

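### The plan for CT and echocardiographic annulus sizing gives separate agreement coefficients, which do not provide the within-patient comparison of the two methods, or the bias in mm, that the Discussion's stated aim needs

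*Protocol article*

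**What the plan says.** The protocol article words this question in two ways.

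- **Discussion:** "Our secondary objective is to compare the reliability of preoperative CT-scan and echocardiography used to assess the size of the aortic annulus", with the surgical measurement as the reference.
- **Objectives of the Trivalve study:** "comparison between the effective aortic orifice area measured by computerized tomography (CT)-scan and echocardiography and the intraoperative measurement performed by a flat-head candle". Table 4 has the same structure, with CT and echocardiography each set against the surgical data, but speaks of a diameter in mm where Objectives speaks of an area.

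The data are paired. Under enrolment, consenting patients "will undergo, preoperatively, a CT-scan and a transthoracic echocardiogram to measure the aortic annulus", and the Surgery section adds a candle reading of the same annulus.

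For these measurements, Statistical analyses plans Pearson or Spearman correlations, and "the Lin concordance coefficient and the intra-class coefficient (ICC) will be calculated". Two other analyses come close but serve other purposes. One is optional and concerns valve arms: "Later on, an ANCOVA could be proposed to consider group effect". The other is a paired test over time: "hemodynamic data by echocardiography on preoperative period and at six months".

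**The concern.** If the aim is to say which imaging method sizes the annulus more reliably, a contrast between CT and echocardiography is needed. Two coefficients computed in the same patients against the same candle reading are correlated. Neither ranking them nor checking whether their separate intervals overlap is a sound comparison. Ranking always puts one method first, even when the two are equal. Waiting for the intervals to part is very insensitive.

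A coefficient also has no unit. It does not tell a surgeon by how many mm a method over- or under-reads, which is what matters when choosing a valve size. At stake is how a secondary, non-randomised measurement question is interpreted.

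**Working it through.** **Plan's own figure.** None is given for this comparison. The sample-size calculation (44, then 55 per group) concerns the gradient and does not bear on it. From it comes only the largest available number of pairs: 3 × 55 = 165.

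**Assumed inputs** (the document gives none): true annulus SD 2.5 mm; candle error SD 0.7 mm unless stated; CT and echocardiography equal truth plus error, with the SDs below.

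**What the Lin coefficient measures.** With annulus variance 2.5² = 6.25, method error SD e, candle error SD s and bias d:

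Lin = 2 × 6.25 / (2 × 6.25 + e² + s² + d²)

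- CT, e = 1.2: 12.5 / (12.5 + 1.44 + 0.49) = 0.87
- Echocardiography, e = 1.6: 12.5 / (12.5 + 2.56 + 0.49) = 0.80

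Mean absolute error against the candle is √(2/π) × √(e² + s²):

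- CT: 0.798 × √1.93 = 1.11 mm
- Echocardiography: 0.798 × √3.05 = 1.39 mm

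**Simulated trials, n = 165, 4,000 data sets per row.** The two right-hand columns give the share of trials in which the separate 95% Lin intervals are disjoint, and the share in which a paired t-test of absolute errors has p < 0.05. Ranges reflect repeated runs.

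| Error SD, CT / echo (mm) | Candle SD (mm) | Error correlation | Intervals disjoint | Paired test |
|---|---|---|---|---|
| 1.5 / 1.5 | 0.7 | 0 | 0% | about 5% |
| 1.2 / 1.6 | 0.7 | 0 | 12–13% | 79–80% |
| 1.2 / 1.6 | 1.0 | 0 | 4–5% | 64–66% |
| 1.2 / 1.5 | 0.7 | 0 | 4% | 56–58% |
| 1.2 / 1.6 | 0.7 | 0.3 | 10% | 84–85% |

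In the first row (equal methods), which coefficient is larger is a coin flip, and the two differ by more than 0.03 in about 25% of trials.

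**A different paired contrast** (bootstrap interval for the difference in Lin coefficients, 600 runs, 300 resamples) points the same way:

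- 1.2 / 1.5 mm: disjoint intervals 4% against 64% detection (correlation 0.3); 2% against 81% (correlation 0.6).
- 1.0 / 1.5 mm, correlation 0.3: 43% against 98%.

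**Bias.** In the formula d is squared, so its sign is lost. With equal SDs of 1.5 mm and biases of +0.5 and −0.5 mm, both methods have Lin = 12.5 / (12.5 + 2.25 + 0.49 + 0.25) = 0.81. The paired Lin contrast then rejects in only 6% of trials. The mean of CT minus echocardiography is 1.0 mm. Its standard error, with independent errors, is √(1.5² + 1.5²) / √165 = 2.12 / 12.8 = 0.17 mm, so the difference is about six standard errors. The simulation detects it in 100% of trials. A contrast of coefficients or of absolute errors is therefore not enough without the signed errors.

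**The case against.** The strongest reply is that the endpoint, as defined in Objectives and Table 4, is each method against surgery. Lin and ICC are standard for that, so the plan answers it. The head-to-head reading rests on one Discussion sentence, which itself ends by referring to the surgical measurement. This stands in part: it would be wrong to say that the secondary objective goes unanswered. It does not remove the mismatch, because the Discussion sentence most naturally compares the two methods and the named analysis does not.

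A reader might also infer that the trial will declare a false winner, or that error control is lost. The document does not support that. It plans no ranking rule, no test and no interval-overlap rule, so there is no planned error rate to lose. The two harms also belong to different habits of reading. Where a real difference in precision was simulated, ranking the point estimates put the better method first in about 98% of trials or more. Real differences are missed only by someone who waits for the intervals to part.

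It is fair, too, that all the error SDs are assumed. A condensed article may leave detail to a fuller plan, but here it names a method for the question, and that method falls short of one stated aim, which is more than silence.

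Finally, Table 3 lists an annulus diameter under CT and under surgery but none under echocardiography, although the enrolment section announces that measurement. The paired analysis depends on that value being recorded.

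**Conclusion.** The point holds in a limited form. The coefficients describe each method's agreement with the candle. They do not give a within-patient comparison of CT with echocardiography or a bias in mm, and one statement of the objective calls for the comparison. Over-reading of equal methods and concealment of a real difference in precision or bias are possible misreadings, not planned errors.

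For assumed error SDs of 1.2 against 1.5 or 1.6 mm (annulus SD 2.5 mm, candle SD 0.7 mm, independent errors, 165 complete pairs), the gap is about 4 to 12% against 56 to 79%. Other SDs, correlated errors or fewer complete pairs would change it. The primary gradient comparison is untouched. This is a cheap improvement, not a flaw that threatens the trial.

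**What to change.** In Statistical analyses, for patients with CT, echocardiographic and candle diameters, using one patient set for both methods:

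1. Report the mean signed error of each method (CT minus candle, echocardiography minus candle) with its 95% confidence interval and limits of agreement.
2. Compare CT with echocardiography within patients, with a 95% confidence interval: either the paired difference in absolute error or a bootstrap difference in Lin coefficients. Add the paired mean difference, CT minus echocardiography.
3. Keep the correlation, Lin and ICC coefficients as description.

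Also align the objective across Objectives, Table 4 and Discussion, including area against diameter, and list the echocardiographic annulus diameter in Table 3. If no head-to-head comparison is intended, reword the Discussion as agreement of each method with surgery. Item 2 is then not needed, but item 1 still is.

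The cost is a few sentences and slightly more analysis on a secondary question. No new measurement is required, provided the echocardiographic annulus diameter is recorded as announced.

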### Statistical considerations

#### Sample size estimation

The estimation of the number of patients required was considered by using previous data provided by the manufacturers on patients who had cardiovascular surgery which showed the mean postoperative gradients (mmHg) for the three studied types of valve (data not published). A minimum difference (δ) of 4 mmHg could be expected between the three types of valve for the most relevant diameters (21 and 23 mm). As the information concerning statistical variability was not provided in this document, the standard deviation (σ) was estimated on the basis of data from 103 patients observed in our center (84 with the Edwards Ease prosthesis, 19 with a Mitroflow diameter of 21 or 23 mm): σ = 5.8. Thus, for a type 1 error α = 0.05 (two-sided), a 90 %-power, δ = 4 and σ = 5.8, 44 subjects per group are needed. Taking into account multiple comparisons between the three randomized groups, 55 patients per group will be included (165 patients in total).

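### No baseline covariate is fixed for comparing the valves on month-6 echo measures: adjustment waits on observed imbalance, and pre/post change is tested only within arms

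*Protocol article*

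**What the plan says.** All of this stands in the Protocol article, mainly under Statistical analyses.

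- **Between valves.** The month-6 mean gradient is compared by ANOVA with Tukey-Kramer, or by Kruskal-Wallis with Dunn's test if the ANOVA conditions fail. Neither has a covariate. Other continuous outcomes follow: "Quantitative secondary endpoints (for example hemodynamic data, CT-scan, in-hospital stay) will be analyzed as described above".
- **Adjustment.** Every between-group comparison is made unadjusted. Where judged suitable, it is repeated in a linear regression on factors that prove unbalanced despite randomization. Echocardiographic features are among the characteristics compared between arms at baseline, so they are candidates for this step.
- **Pre/post change.** "The intra-group comparisons related to the quantitative criteria (hemodynamic data by echocardiography on preoperative period and at six months) will be made using" a paired ANOVA or Wilcoxon test.
- **A possible ANCOVA.** One sentence leaves open a later ANCOVA for group effect. It follows the text on agreement between sizing methods and names neither outcome nor covariate.
- **Data.** Table 3 schedules ventricular diameters, wall thicknesses, shortening and ejection fraction, pulmonary pressure, cardiac output, gradients and orifice area before surgery, at day 7 and at month 6.

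**The concern.** The trial exists to compare three valves. The preoperative echo values could sharpen that comparison, yet the only analysis certain to use them as a pre/post contrast runs inside each arm. Such a test sets randomization aside. For gradient and orifice area it contrasts a diseased native valve with a prosthesis, so it mainly shows that replacement works.

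The conditional adjustment does not fill the gap, because it selects covariates by observed imbalance. The precision gained from a baseline covariate depends on how well it predicts the outcome, and it is available when the arms are perfectly balanced, which is exactly when this rule leaves the covariate out. The adjusted model also stays undefined until the baseline data have been inspected.

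At stake are wider confidence intervals than necessary for the valve differences, a covariate list that depends on the data, and three separate within-arm p-values that could be misread as a comparison.

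**Working it through.** **1. The plan's own figure, without a covariate.** Inputs from Sample size estimation: "for a type 1 error α = 0.05 (two-sided), a 90 %-power, δ = 4 and σ = 5.8, 44 subjects per group are needed".

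n per group = 2 × [σ(z₀.₉₇₅ + z₀.₉₀)/δ]² = 2 × [5.8 × (1.960 + 1.282)/4]² = 44.18. The stated 44 reproduces (45 if rounded up).

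With a Bonferroni correction for three pairs (α = 0.05/3), the same formula gives 57, close to the 55 planned. At 55 per group, with Tukey's critical value, pairwise power is 89.3%. The unadjusted design therefore delivers about what it promises.

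**2. What a baseline covariate would add.** Let r be the correlation between a measure's preoperative and month-6 values. The residual SD becomes σ√(1 − r²), so variance falls by r². The unadjusted arm size giving the same precision as 55 adjusted patients is 55/(1 − r²). The protocol does not give r, so the range below is an assumption.

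| r | Variance cut (r²) | Confidence interval narrower by 1 − √(1 − r²) | 55/(1 − r²) |
|---|---|---|---|
| 0.1 | 1% | 0.5% | 55.6 |
| 0.3 | 9% | 4.6% | 60.4 |
| 0.5 | 25% | 13.4% | 73.3 |
| 0.7 | 49% | 28.6% | 107.8 |

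**3. The same range on the primary endpoint** (δ = 4, σ = 5.8, 55 per group, Tukey pairwise power):

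| r | Residual SD | Power |
|---|---|---|
| 0 | 5.80 | 89.3% |
| 0.1 | 5.77 | 89.7% |
| 0.3 | 5.53 | 92.2% |
| 0.5 | 5.02 | 96.4% |
| 0.7 | 4.14 | 99.6% |

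The preoperative gradient belongs to the valve that is removed, so the upper rows may be the relevant ones here. Ventricular measures describe the same ventricle before and after surgery, so the lower rows are more plausible for them. The protocol gives neither δ nor σ for those measures, so only the table in step 2 applies.

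**4. Why within-arm p-values cannot stand in for a comparison.** Suppose all three valves have the same true change and each within-arm test has power p. The arms disagree on significance with probability 1 − p³ − (1 − p)³:

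- p = 0.5: 1 − 0.125 − 0.125 = 75%
- p = 0.6: 1 − 0.216 − 0.064 = 72%
- p = 0.8: 1 − 0.512 − 0.008 = 48%
- p = 0.9: 1 − 0.729 − 0.001 = 27%

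The power values are assumptions. For gradient, where relief of stenosis should be large, p may be close to 1 and disagreement close to 0.

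**The case against.** A reader might infer that the preoperative echo values never enter a valve comparison. The document does not support that. Echo features are checked at baseline, unbalanced factors may be adjusted for by regression, and the secondary haemodynamic data follow the same two-step scheme. What stands against the plan is narrower: entry of the covariate is conditional and settled after the data are seen.

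A reader might also infer that the within-arm tests will be used to rank the valves. No sentence says so. They are labelled as within-group, and a separate between-group test is given. The risk is misreading at the reporting stage, not a stated intention.

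The best remaining objections concern size. The unadjusted ANOVA is valid with 1:1:1 randomization and matches the sample-size basis. All secondary endpoints are said to be in Table 4, which lists no ventricular dimension, wall thickness or ejection fraction, so the largest gains fall on measures outside the listed endpoints. For the listed gradient and orifice-area endpoints, the gain may be a few percent. These objections stand and limit the weight of the point.

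It could also be said that covariate lists belong in an analysis plan that is not shown. That does not remove the point, because the article does state an adjustment rule and a pre/post method, and the criticism is of those two choices.

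**Conclusion.** The point holds as a matter of efficiency and prespecification. No baseline covariate is fixed for the month-6 valve comparisons, adjustment depends on observed imbalance, and pre/post change is tested only within arms, which does not compare valves. The primary test is not biased, and the sample size is not called into question.

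The loss is r² of the residual variance: from 1% (r = 0.1) to 49% (r = 0.7). This rests wholly on an assumed r. That r is lower for gradient and orifice area than for ventricular measures is likewise a judgement, not something the document reports. The disagreement rates of 27% to 75% rest on assumed within-arm power and serve only to show why separate p-values are not a comparison. This is an improvement worth making because it costs nothing, not a flaw that threatens the main result.

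**What to change.** 1. Replace the imbalance-triggered adjustment with a prespecified linear model for each continuous echo measure recorded both before surgery and at month 6: month-6 value on valve group plus its own preoperative value and, if wanted, the preoperative CT annulus diameter. Paravalvular leak has no preoperative value and regurgitation is graded 0–4, so this model does not suit them.
2. Report Tukey-adjusted pairwise valve differences with 95% confidence intervals from that model. State beforehand whether it or the unadjusted ANOVA leads for the primary endpoint.
3. Report within-arm pre/post changes descriptively, and state that they are not used to compare valves.

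The cost is analysis wording only. Table 3 already schedules every variable, and no additional patients, visits or measurements are needed. The wording should be settled before outcome data by arm are examined.
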